#### Sample size and statistical analysis

This trial will recruit 120 participants (60 participants per group) to confirm the primary outcome equivalence between biportal endoscopic and conventional decompressive laminectomy. Previous studies have indicated a minimal clinically important ODI difference of 12.8 [17], as well as a standard deviation of 18.8, at 1 year after endoscopic decompressive laminectomy [18]. A required sample size of 60 patients per group was determined based on these values and the following parameters: alpha of .05, power of .90, two-sided confidence interval of 95%, and a 20% loss to follow-up.

All statistical analyses will be performed using SPSS 26.0 (version 26.0, Chicago, IL, USA). A *P* value < .05 will be considered significant. A modified intention-to-treat (mITT) analysis will be used. The mITT strategy indicates that participants are analyzed on whether they underwent a randomly assigned surgery (to avoid the effects of crossover and dropout, which may disrupt the random assignment to the treatment groups). Participants who do not complete the follow-up schedule will be excluded from the analysis, and there will be no additional enrollment.

In each group, changes in secondary outcomes from baseline to follow-up will be analyzed with repeated measures analysis of variance. Differences in other clinical and radiologic outcomes, as well as adverse events, between the two groups will be analyzed using Student’s t-test (for continuous variables) and chi-square test (for categorical variables).

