**Discussion:**

It is hypothesized that the efficacy and safety of biportal endoscopic and conventional decompressive laminectomy will be comparable in patients with lumbar spinal stenosis. The results of this trial will provide a high level of evidence for the efficacy and safety of the biportal endoscopic technique in patients with lumbar spinal stenosis and facilitate the development of clinical practice guidelines. Furthermore, the results of this study may indicate the feasibility of the biportal endoscopic technique for other types of spinal surgery.

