Previous studies evaluating the use of the biportal endoscopic technique in LSS surgery have reported good clinical results; however, the strength of evidence has been limited by the use of a retrospective study design and small sample sizes [10, 11]. There is currently a lack of level 1 studies to establish the efficacy and stability of the biportal endoscopic technique in comparison with conventional methods. Therefore, we aim to compare the efficacy and safety of biportal endoscopic decompressive laminectomy with those of conventional decompressive laminectomy in a multicenter, prospective randomized controlled trial (RCT). Our hypothesis is that the efficacy and safety of these two methods are similar in patients with LSS.

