### Outcome measures

#### Primary outcome

The primary outcome will be the difference in Oswestry Disability Index (ODI) scores between baseline and at 1 year after surgery [14]. Among the wide range of patient-reported outcomes, the ODI is the most suitable for functional evaluation of the lumbar spine. Patients are instructed to provide an answer of 0–5 for each section in the ODI questionnaire, with a score of 5 representing the greatest disability. The total score is calculated as a percentage of the total maximum score (excluding questions with no responses). In cases where a patient provides two or more responses to a single question, the highest score will be counted.

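### The trial is meant to confirm equivalence in ODI, but the only decision criterion stated is P < .05, with no margin, confidence-interval rule or test for the primary comparison

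*Protocol article*

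**What the plan says.** The aim is worded as equivalence throughout. Under Sample size and statistical analysis, 120 participants are recruited "to confirm the primary outcome equivalence between biportal endoscopic and conventional decompressive laminectomy". The Background section states: "Our hypothesis is that the efficacy and safety of these two methods are similar in patients with LSS". The Discussion part of the abstract says: "It is hypothesized that the efficacy and safety of biportal endoscopic and conventional decompressive laminectomy will be comparable". The primary endpoint is defined under Primary outcome: "The primary outcome will be the difference in Oswestry Disability Index (ODI) scores between baseline and at 1 year after surgery".

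The sample-size paragraph gives these inputs: "Previous studies have indicated a minimal clinically important ODI difference of 12.8", "as well as a standard deviation of 18.8, at 1 year after endoscopic decompressive laminectomy", alpha .05, power .90, a two-sided 95% CI and 20% loss to follow-up. The result is 60 per group.

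The only criterion for a conclusion is that a P "value < .05 will be considered significant", stated without restriction to particular outcomes. Repeated measures ANOVA is assigned to within-group changes in secondary outcomes. Student's t-test and chi-square are assigned as follows: "Differences in other clinical and radiologic outcomes, as well as adverse events, between the two groups will be analyzed". No test is named for the primary ODI comparison. The article contains no equivalence margin so called, no rule comparing a CI with a margin, and no two one-sided tests (TOST) procedure.

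**The concern.** The stated criterion is of the wrong kind for the stated aim. A difference test at P < .05 can give evidence that two operations differ. When it fails to do so, it gives no evidence that they are alike, because the failure may only reflect a wide CI. An equivalence claim needs a margin and a demonstration that the data exclude differences beyond it. The article has a candidate margin (12.8) and a CI level, but connects neither to a conclusion.

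At stake is the error rate that matters most here: concluding that the operations are comparable when they differ by a clinically important amount. Under a CI-within-margin rule that rate is fixed in advance. Under P >= .05 it depends on how many patients remain for analysis and rises as they are lost. The analysis section excludes patients who do not complete follow-up and allows no replacement, so the number analysed is not guaranteed.

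**Working it through.** **Inputs.** From Sample size and statistical analysis: d = 12.8, SD = 18.8, alpha .05, power .90, 20% loss, 60 per group. Allocation is 1:1 (Randomization). Evaluable per group as planned: 60 × 0.8 = 48. Assumptions of this check: 12.8 serves as the margin, SD is 18.8 in both groups, and power for equivalence is computed at a true difference of 0.

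**Step 1: reproduce the plan's 60 per group.**
- Two-sided difference test at .05: n = 2 × (18.8 × (1.960 + 1.282) / 12.8)² = 45.3, so 46; 46 / 0.8 = 57.5, so 58. With the t distribution: 47, so 59.
- Equivalence, TOST at one-sided .05 each (90% CI): n = 2 × (18.8 × (1.645 + 1.645) / 12.8)² = 46.7, so 47; 47 / 0.8 = 58.75, so 59. With the t distribution: 48 / 0.8 = 60.
- Equivalence, TOST at one-sided .025 each (95% CI): n = 2 × (18.8 × (1.960 + 1.645) / 12.8)² = 56.1, so 57; 57 / 0.8 = 71.25, so 72. With the t distribution: 58 / 0.8 = 72.5, so 73.

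The stated 60 is therefore not an arithmetic error. It fits a difference test or a 90% CI equivalence test, and so does not show which was intended. It does not fit equivalence judged on the 95% CI that the paragraph lists.

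**Step 2: thresholds on the observed difference, 48 per group.**
- SE = 18.8 × √(2/48) = 3.84, with 94 degrees of freedom.
- P >= .05 when |difference| < 1.986 × 3.84 = 7.6.
- 95% CI within ±12.8 when |difference| < 12.8 − 7.6 = 5.2.
- 90% CI within ±12.8 when |difference| < 12.8 − 1.661 × 3.84 = 12.8 − 6.4 = 6.4.

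An observed difference between 5.2 (or 6.4) and 7.6 is non-significant yet does not show equivalence.

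**Step 3: probability of each result, 48 per group** (noncentral t for P >= .05; exact integration over the sample SD for the CI rules).

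| True difference | P >= .05 | 90% CI within ±12.8 | 95% CI within ±12.8 |
|---|---|---|---|
| 0 | 95% | 90% | 82% |
| 8 | 46% | 34% | 23% |
| 10 | 27% | 18% | 11% |
| 12.8 | 9.0% | 5.0% | 2.5% |

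**Step 4: dependence on the number analysed, true difference 12.8.** If all 60 per group are evaluable, P >= .05 occurs in 4.1%. At the planned 48 it is 9.0%. In a hypothetical case of 30 per group (50% loss, well beyond the planned 20%) it is 26%. The CI rules stay at or just under 5.0% and 2.5% throughout. With no true difference, P >= .05 stays at 95% whatever the number analysed, while the chance of meeting the 95% CI rule falls from 82% at 48 to 47% at 30. Losing patients costs nothing under P >= .05 and is penalised under a CI rule.

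**The case against.** The strongest defence is that the article does not prescribe the error. The t-test and chi-square are assigned to outcomes other than the primary one, and the P < .05 sentence is generic enough to cover the P values of TOST. The ingredients of an equivalence rule share one paragraph: an equivalence aim, 12.8 points, alpha, power and a two-sided CI. TOST at one-sided .05 with the t distribution gives exactly 60 per group. The rule itself might stand in a full protocol or SAP that is not shown.

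Much of this stands. A reader might infer that the investigators will run a t-test on ODI and report a non-significant result as equivalence. The document does not say so. No test is named for primary ODI, and nowhere is non-significance said to mean equivalence. Nor does it follow that the primary question cannot be answered: the planned data can answer it once a rule is written down. The 26% figure belongs to a hypothetical loss, not to the plan.

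What does not stand is that the equivalence rule is already there. The 12.8 is labelled a minimal clinically important difference and the CI a sample-size parameter; neither is tied to a conclusion. Reading the listed 95% CI as the criterion requires 72 to 73 per group, not 60. Since 60 also fits a difference test (58 to 59), it cannot settle the intention. The article does more than stay silent: it states one unrestricted criterion, and as a difference criterion that does not match the aim.

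**Conclusion.** The point holds in this form: the trial is set up to confirm equivalence in ODI, but the article states only P < .05 as a criterion, with no margin, CI rule or test for the primary comparison. If P >= .05 were taken as support for equivalence, then at 48 evaluable per group a true difference equal to the full 12.8 points would pass in 9.0% of trials, against 5.0% (90% CI) or 2.5% (95% CI) under a proper rule. At a true difference of 10 points the figures are 27% against 18% or 11%. The excess depends on losses: at a full 60 per group P >= .05 passes 4.1%, slightly below the 90% CI rule, and the gap widens as patients are lost.

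These figures rest on SD 18.8 in both groups, 12.8 as the margin, and a simple comparison of two means. The mismatch between aim and criterion rests on none of them. It should be fixed before analysis, because the choice of margin and CI level decides what result counts as success.

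**What to change.** For the primary ODI comparison, state that equivalence is concluded only if the CI for the between-group difference lies entirely within -12.8 to +12.8, and state the CI level. Keep P < .05 for difference hypotheses on other outcomes. Add that a non-significant difference will not be interpreted as equivalence.

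The cost is a few sentences in the article's analysis section and the SAP, and it depends on the CI level:
- 90% CI (TOST at one-sided .05): the planned 60 per group, 48 evaluable, keeps about 90% power. No additional patients are needed, but the 95% CI in the sample-size paragraph must be reconciled with this choice.
- 95% CI, as now listed: power with 48 evaluable per group is about 82% and should be restated as such. Restoring 90% would take 57 to 58 evaluable, that is 72 to 73 per group or 144 to 146 in total.

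Under either choice equivalence is harder to claim than under P >= .05 at the planned 48 per group.

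### The stated two-sided 95% confidence interval, 90% power, 20% loss and 60 per group cannot all hold for the equivalence objective

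*Protocol article*

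**What the plan says.** The section Sample size and statistical analysis says that 120 participants, 60 per group, are recruited "to confirm the primary outcome equivalence between biportal endoscopic and conventional decompressive laminectomy". The inputs are a "minimal clinically important ODI difference of 12.8" and "a standard deviation of 18.8, at 1 year after endoscopic decompressive laminectomy". The remaining parameters are "alpha of .05, power of .90, two-sided confidence interval of 95%, and a 20% loss to follow-up". The same section excludes participants who do not complete the follow-up schedule and rules out additional enrolment. If the planned loss occurs, 60 × 0.8 = 48 per group are analysed.

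The text does not name an equivalence margin or a true difference. The 12.8 is the only difference in the calculation. The Background gives the hypothesis that the two methods are similar.

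**The concern.** In an equivalence comparison, the confidence level sets the stringency of the test. Requiring a two-sided 95% interval to lie inside the margin amounts to two one-sided tests at .025 each; requiring a 90% interval amounts to two at .05 each. The sentence gives both an alpha of .05 and a 95% interval without saying which governs the equivalence test, and the two lead to different sample sizes.

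Two things are at stake. If the 95% interval is the criterion, the trial has less power than it states. And if the level stays open until the data are in, a result whose 90% interval lies within ±12.8 while its 95% interval does not could be read either way.

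**Working it through.** **Inputs from the protocol article.** SD 18.8; difference 12.8; alpha .05; power .90; two-sided 95% interval; 20% loss; 60 per group (all from Sample size and statistical analysis); 1:1 allocation (Randomization).

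**Assumptions, not stated in the document.** 12.8 is the equivalence margin; 18.8 is the SD of the analysed ODI variable; the true difference is 0, the most favourable case.

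**Formula.** For two one-sided tests (TOST) at level a each, with true difference 0:

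n per group = 2 × (z(1−a) + z(1−β/2))² × SD² / margin²

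Here β = .10, so z(1−β/2) = 1.645, and SD²/margin² = 353.44/163.84 = 2.157. Randomised number = n / 0.8. The t-based figures integrate the power over the distribution of the sample variance.

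**1. Reproducing 60 per group.**

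| Calculation | Evaluable per group, normal | Evaluable per group, t-based | Randomised per group |
|---|---|---|---|
| TOST at .05 per side (90% interval) | 2 × (1.645 + 1.645)² × 2.157 = 46.7 → 47 | 48 | 59; **60** |
| Two-sided superiority test at .05 | 2 × (1.960 + 1.282)² × 2.157 = 45.3 → 46 | 47 | 58; 59 |
| Non-inferiority, one-sided .025 | 46 | – | 58 |
| TOST at .025 per side (95% interval, as stated) | 2 × (1.960 + 1.645)² × 2.157 = 56.1 → 57 | 58 | 72; 73 |

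Of these, only the t-based TOST at .05 per side gives 60 exactly (48 / 0.8 = 60). The superiority and non-inferiority formulas come within two patients. The stated combination, equivalence with a 95% interval, is 12–13 per group away. Inflating by multiplying by 1.2 instead of dividing by 0.8 does not close the gap: it gives 69–70.

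**2. Power with 48 evaluable per group.**

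Standard error = 18.8 × √(2/48) = 3.838, and 12.8 / 3.838 = 3.335.

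- 95% interval, normal: 2Φ(3.335 − 1.960) − 1 = 83.1%; t-based 82.0%.
- 90% interval, normal: 2Φ(3.335 − 1.645) − 1 = 90.9%; t-based 90.4%.

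**3. Sensitivity to the true difference (95% interval, 48 per group).**

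| True difference (ODI points) | t-based | Normal |
|---|---|---|
| 0 | 82.0% | 83.1% |
| 1 | 80.6% | 81.7% |
| 2 | 76.4% | 77.5% |
| 3 | 69.8% | 70.8% |

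**4. Sensitivity to loss.** With no loss, 60 per group give 91.8% (t-based) with a 95% interval. The t-based power is 89.97% at 57 and 90.6% at 58 evaluable per group. Ninety per cent is therefore reached only if 57–58 of the 60 are evaluable, a loss of about 3–5% rather than 20%.

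**The case against.** The strongest reply is that 60 is right and only the interval level is mislabelled. Equivalence, alpha .05 per side, 90% power, 20% loss and 60 per group fit together exactly, and quoting 95% where 90% is meant is an easy slip with two one-sided tests. This stands as far as it goes. A reader might infer from the mismatch that the sample size is an arithmetic error, or that the trial simply lacks its 90% power; the document supports neither, because under a 90% interval the power is as stated. But the sentence says 95%, so the contradiction remains until one of the figures changes.

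A reader might also infer an 18% risk of missing equivalence between identical operations. That risk applies only if the 95% interval is the criterion. The article gives the interval as a sample-size parameter and, for the analysis, mentions only a *P* value threshold of .05; it contains no interval-based decision rule. A statistical analysis plan may supply one, and its absence here is not the complaint. An unseen plan cannot make the article's stated level, power, loss and sample size agree.

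The assumptions also matter. The article calls 12.8 a minimal important difference, not a margin; a smaller margin would widen the shortfall. It gives 18.8 as an SD at 1 year, whereas the Primary outcome section defines a difference from baseline. If, as an assumption, the SD is equal at both times, the SD of the change is 18.8 × √(2(1 − r)): 22.2 at a baseline correlation r of 0.3, with about 59% power under a 95% interval, and 16.8 at r = 0.6, with about 92%. The document gives no correlation, so 82% is the power under the plan's own inputs, not a forecast. For the same reason it cannot be claimed that baseline adjustment would make up the difference.

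Finally, lower power does not bias the estimate or inflate the type I error. That is correct, and it limits the consequence.

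**Conclusion.** The sentence is wrong as written: its parameters cannot all hold. On the article's own figures, with 12.8 as margin, 18.8 as the SD of the analysed variable and no true difference, 48 evaluable per group give about 82% power with a two-sided 95% interval, 8 percentage points below the stated 90%. Keeping both the 95% interval and 90% power would take 72–73 randomised per group instead of 60.

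The finding is an inconsistency between confidence level and power. Which of the two was intended cannot be settled from the article, although the exact match at .05 per side makes a 90% interval a plausible intention.

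**What to change.** Before results are known, reconcile the sample-size sentence in one of two ways, and say in it that 12.8 is the equivalence margin, if so intended:

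- **(a) Keep the two-sided 95% interval** and restate the power: 48 evaluable per group give about 82% power to place the interval within ±12.8, assuming an SD of 18.8 and no true difference.
- **(b) If two one-sided tests at .05 each were intended**, replace 95% with 90% and name the 90% interval as the equivalence criterion. Sixty per group and 90% power are then correct under the same assumptions.

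Either way the cost is one sentence. Under (a) the stated power becomes less favourable; under (b) the interval level is corrected. The sample size stays at 60 per group in both.

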**Methods:**

This study will include 120 patients (60 per group, aged 20–80 years) with 1- or 2-level lumbar spinal stenosis, who will be recruited from six hospitals. The study will be conducted from July 2021 to December 2024. The primary outcome (Oswestry Disability Index at 12 months after surgery) will be evaluated through a modified intention-to-treat method. The secondary outcomes will include the following: visual analog scale score for low back and lower extremity radiating pain, EuroQol 5-dimensions score, surgery satisfaction, walking time, postoperative return to daily life period, postoperative surgical scars, and some surgery-related variables. Radiographic outcomes will be analyzed using magnetic resonance imaging or computed tomography. All outcomes will be evaluated before the surgery and at 2 weeks, 3 months, 6 months, and 12 months postoperatively. This protocol adheres to the Standard Protocol Items: Recommendations for Interventional Trials (SPIRIT) guidelines for reporting of clinical trial protocols.

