#### Secondary outcomes

##### Clinical outcomes

Visual analog scale (VAS) score for low back pain and radiating pain of the lower extremities: scores range from 0 to 10; a higher score indicates more severe painPatient’s quality of life, as assessed by the EuroQol 5-dimensions questionnaire (EQ-5D): EQ-5D contains five questions with five responses for each question, and the total score is converted into the final EQ-5D value, ranging from 0.000 to 1.000; higher score indicates a better quality of life [15].Surgery satisfactionWalking timePostoperative return to daily life periodSurgical scars, as evaluated using the Patient and Observer Scar Assessment Scale 2.0, which contains six parameters with 10-point scoring system; 6 represents normal skin and 60 represents the worst scar imaginableSurgery-related variables, such as postoperative drainage (mL), operation time (minutes), admission duration (hours), and postoperative creatine kinase (International Unit/L)

Patient-reported outcomes will be collected from the participants at baseline and at 2 weeks, 3 months, 6 months, and 12 months after surgery.

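### The only stated analysis set for the primary outcome selects patients on events after randomisation, is labelled modified intention-to-treat, and is justified by a reversed rationale

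*Protocol article*

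**What the plan says.** The section Sample size and statistical analysis names a single analysis set: "A modified intention-to-treat (mITT) analysis will be used". The abstract ties it to the primary outcome, which "will be evaluated through a modified intention-to-treat method".

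Two rules define the set:

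- **Treatment received:** "participants are analyzed on whether they underwent a randomly assigned surgery". The reason given is "to avoid the effects of crossover and dropout, which may disrupt the random assignment to the treatment groups".
- **Completion:** "Participants who do not complete the follow-up schedule will be excluded from the analysis, and there will be no additional enrollment".

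Under Primary outcome, the endpoint needs two time points only: "The primary outcome will be the difference in Oswestry Disability Index (ODI) scores between baseline and at 1 year after surgery". The schedule is longer. Under Clinical outcomes, patient-reported measures are taken "at baseline and at 2 weeks, 3 months, 6 months, and 12 months after surgery", and Table 1 shows ODI at all four postoperative visits.

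The stated aim is equivalence on the primary outcome. The article mentions no all-randomised analysis, and the completion rule as worded leaves no room for one.

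**The concern.** Randomisation fixes the assigned groups, and nothing that happens later can undo that. Crossover and dropout are outcomes of the trial process and may depend on the arm and on how the patient is doing. Removing or regrouping patients because of them replaces the randomised comparison with a selected one, so the article's reason for the rule runs the wrong way round.

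Three features of this trial make the selection more than a formality:

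- The Discussion describes a steep learning curve for the endoscopic technique (about 58 cases) and cites complications in 7 of 68 cases (10.3%) during it. Sixteen surgeons take part.
- Patients know their allocation after surgery and ODI is self-reported, so loss to follow-up can be related to arm and to outcome.
- The claim is equivalence. A per-protocol set has a recognised place in such trials beside an as-randomised analysis, but not as the only analysis, and not under an intention-to-treat type of name.

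The completion rule may also discard observed primary data, because a patient can have a 12-month ODI and still have missed an earlier visit.

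**Working it through.** **1. The plan's own sample size.** Inputs from the article: difference 12.8, SD 18.8, alpha .05, power .90, 95% two-sided confidence interval, 20% loss, 60 per group.

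- Difference test: n = 2 × [18.8 × (1.960 + 1.282) / 12.8]² = 45.3, so 46; 46 / 0.8 = 57.5, so 58.
- Two one-sided tests (TOST), true difference 0, .05 per side: n = 2 × [18.8 × (1.645 + 1.645) / 12.8]² = 46.7, so 47; 47 / 0.8 = 58.75, so 59.
- TOST at .025 per side, which matches a 95% interval: n = 2 × [18.8 × (1.960 + 1.645) / 12.8]² = 56.1, so 57; 57 / 0.8 = 71.25, so 72.

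The stated 60 is reproduced closely by the first two and not by the third. A 20% loss is already budgeted, leaving 48 per group.

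**2. What the rules do to the set.**

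| Rule | Reading | Consequence |
|---|---|---|
| Assigned surgery undergone | Crossovers excluded (most natural, given the stated purpose) | Selected on treatment received; not intention-to-treat |
| Assigned surgery undergone | Grouped by operation received | As-treated; not intention-to-treat |
| Schedule completed | All four visits (literal) | Completer set; some observed 12-month ODI discarded |
| Schedule completed | Only loss before 12 months meant | Completer set; no observed 12-month ODI discarded |

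On these readings the set is selected on what happened after randomisation.

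**3. Size of the bias.** Let a fraction f of an arm be excluded, with a mean ODI change G points worse than those kept. The arm mean then shifts by f × G, and the between-group difference shifts by f_E × G_E − f_C × G_C (E endoscopic, C conventional). The article gives neither f nor G, so these are assumptions, with exclusions in one arm only:

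- f = 10%, G = 10: 0.10 × 10 = 1.0 point.
- f = 10%, G = 20: 0.10 × 20 = 2.0 points; 2.0 / 12.8 = 16%.
- f = 20%, G = 10: 0.20 × 10 = 2.0 points.

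If both arms lose patients, the terms partly cancel or change sign, so the direction is not fixed.

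**4. Numbers lost under the literal completion rule.** Assume each of four visits is missed independently with probability p. Completers per group are 60 × (1 − p)⁴; patients with a 12-month ODI are 60 × (1 − p).

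| p (assumed) | Completers per group | With 12-month ODI per group | Observed 12-month ODI discarded, of 120 |
|---|---|---|---|
| 3% | 53.1 | 58.2 | 10 |
| 5% | 48.9 | 57.0 | 16 |
| 10% | 39.4 | 54.0 | 29 |

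**5. Power at those sizes** (t-based, 12.8 as the difference or margin, SD 18.8, true difference 0 for TOST).

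| n per group | Difference test | TOST .05 per side | TOST .025 per side |
|---|---|---|---|
| 57 | 0.95 | 0.95 | 0.90 |
| 49 | 0.92 | 0.91 | 0.83 |
| 39 | 0.84 | 0.82 | 0.69 |

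**The case against.** **A per-protocol set is legitimate in equivalence trials.** True, and it should stay. The fault is that it stands alone and carries another name.

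**The definition is printed beside the label.** In the main text that softens the charge of mislabelling. It does not help a reader of the abstract, where only the label appears.

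**The wording is unclear.** This stands. That crossovers are dropped is an inference from an awkward sentence, and that observed 12-month data are discarded follows only if the schedule means all four visits. The neighbouring mentions of dropout, loss to follow-up and no further enrolment make the milder reading possible. Neither milder reading gives an intention-to-treat analysis.

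**The trial is not thereby underpowered.** This stands in large part. A reader might infer that power falls from 90% to 83%. That figure needs independent missed visits at 5% each and TOST at .025 per side, which is not the calculation that reproduces 60 per group. An 18.5% exclusion (1 − 0.95⁴) lies within the budgeted 20%, and under the other two methods power at 49 stays above .90. Missed visits also tend to cluster in the same patients, and the wide later windows in Table 1 (±4 and ±8 weeks) make missed visits less likely. Only the 10% scenario falls below .90 by every method.

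**The bias need not favour the endoscopic arm.** This stands. A reader might infer that failed endoscopic cases vanish and push the result toward equivalence. The article gives no crossover rate and does not mention conversion to open surgery. Crossover before surgery is limited because randomisation is at the operation visit and surgeons learn the allocation immediately beforehand. Differential loss in the control arm could act the other way.

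**Conclusion.** The concern holds in limited form. The article affirmatively fixes one set for the primary outcome, so this is not a detail left to an analysis plan that is not shown, and nothing elsewhere in the article corrects it. The set selects patients on events after randomisation, its label suggests otherwise, and the reason given is reversed.

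The main harm is bias of unknown direction, plus mislabelling. Under the assumed scenarios above the bias is 1 to 2 ODI points against 12.8: modest, but not something that the stated analysis could detect or bound. Loss of observed 12-month data is real only on the literal reading. Power loss is secondary and depends on the assumed missed-visit rate and on the TOST alpha. Because the rule decides who counts in the only stated primary analysis, it should be changed before the data are analysed.

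**What to change.** 1. Delete the completer exclusion.
2. Define the primary analysis as all randomised patients in the group assigned, whatever operation was performed.
3. Use every observed ODI in a likelihood-based mixed model over the scheduled visits, with the 12-month between-group contrast as primary. Multiple imputation is an acceptable alternative.
4. Patients with no post-baseline ODI add little or nothing to such a model, so cover them in a stated sensitivity analysis. The set then remains all randomised patients.
5. Keep the current set as a supporting analysis named per-protocol or completer, and say plainly whether crossovers are excluded or regrouped and which visits count as completion. Require it to agree with the primary analysis before equivalence is claimed.
6. Correct the rationale sentence and the label in the abstract.

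Cost: revised wording and one extra analysis. Crossovers must be followed on the existing schedule. No new visits or patients are needed.
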